###### Faces task

3.2.4.4.1

We will collect a computerized behavioral faces task that consists of angry, happy and surprised face stimuli drawn from the racially diverse affective expression (RADIATE) dataset (Conley et al., 2018). This task design is adapted from prior work investigating valence bias and behavioral markers of tolerance of ambiguous threat (VanTieghem et al., 2017; Saragosa-Harris et al., 2023). The behavioral task design for this study follows the behavioral categorization task design specifications from Saragosa-Harris et al. (2023) with minor language changes to the valence labels. In brief, participants will view surprised (ambiguous), angry (negative), and happy (positive) faces across ten blocks (10 surprised, 5 happy, and 5 angry faces in each block; stimulus presentation for 500ms) and will be asked to indicate whether the face/person in the image is “positive” or “negative” by pressing a button on the keyboard (“1” or “0”, counterbalanced; response screen prompt 1500ms). After each trial response, there will be a 200ms fixation cross and in between each block there will be a 10 s fixation cross. Participants will be trained with feedback prior to completing this task using six practice trials (2 happy, 2 angry, and 2 surprised) that include novel images from a separate dataset (Tottenham et al., 2009). Feedback will not be included in the actual task.

#### Biospecimen samples & measurements

3.2.5

##### Inflammation

3.2.5.1

Non-fasting dried blood spot samples will be collected in the RISE-Up-EA follow up study using Tasso M-20 and T-20 microfluid devices (Tasso, Inc., Seattle, WA, USA) (Wixted et al., 2022). The RISE-Up-EA follow up study will also collect self-report medical history, acquire current medication usage, and health behaviors such as alcohol, smoking, and drug use. If blood samples were not collected at the follow up study (RISE-Up-EA), participants will have the option to provide blood samples at this extension study (RISE-Up-EA+) during the in-person visit. If blood is collected at the extension study visit, we additionally collect information on recent illness and/or vaccines during sample collection. Once collected, samples will be dried, transferred to a biohazard bag with a desiccant, and stored in a −80° Celsius freezer until they are ready to be assayed to preserve protein and nucleic acid biomarkers. These samples will be assayed for pro-inflammatory gene expression profiles, specifically conserved transcriptional response to adversity (CTRA), as well as C-reactive protein (CRP), a systemic peripheral marker of inflammation. Importantly, we are not assessing acute inflammatory responses, effects, or reactivity. Instead, we are identifying more “trait-like” immune profiles by leveraging gene expression and circulating markers indicating systemic inflammation to understand striving-related stress experiences and health-related mechanisms.

##### Microbiome

3.2.5.2

Gut microbiome samples will also be collected in this study. We will administer the OMNIgene OMR-200 stool collection kits (DNAGenotek) to index gastrointestinal microbiome. These stool samples will be collected at home and mailed back to the lab. Briefly, participants will collect a pea size amount of stool using a toilet hat and spatula. A bead homogenizes the sample into a solution which stabilizes the DNA at ambient temperature for 60 days. Once mailed back to the lab, the sample will be stored in a −80° Celsius freezer until samples are ready for DNA extraction and sequencing.

##### ApoE genotype

3.2.5.3

Buccal cell samples will be collected using a buccal swab kit (BHD400b) from Boston Heart Diagnostics in order to assess *ApoE* genotype. The dried blood spot samples are not used to assess *ApoE* genotype because all of the wells are needed for immunoassays for CTRA and CRP, which is why we collect a buccal cell sample. Immediately after collection, samples will be mailed directly to Boston Hear Pre-Analytics. Participants will be classified dichotomously based on the number of *ε4* alleles: none (*ε4-*) versus 1 or 2 (*ε4+*). *ε2/ε4* participants will be excluded from analysis due to the opposing associations between the *ε2* and *ε4* alleles and cognition (Berge et al., 2014).

##### Supplemental health measure: oral microbiome

3.2.5.4

While not part of the initial study design, we will collect an oral microbiome sample as a supplemental health measure to assess an additional pathway where educational experiences might modify health outcomes given preliminary evidence showing that communities of oral microbes and bacteria (Liu et al., 2023; Guo et al., 2023) as well as periodontal inflammatory metrics (Melo et al., 2025) have been altered in AD. OMNIgene OM-501 samples (DNAGenotek) will be administered during the in person visit after the scan ensuring the participants have not ingested food or water for at least 30 minutes prior to the sample. Samples will be incubated at 50 °C for 2h, vortexed, aliquoted into cryogenic tubes and then frozen at −80 °C after these preprocessing steps in lab to prepare them for shipment to the sequencing site. In addition, we will administer an adapted version of the Oral Health Questionnaire (Simpson et al., 2020) to participants to assess overall oral health, including oral hygiene behaviors and symptoms, in order to compute a total oral hygiene score (Buunk-Werkhoven et al., 2011) to be included as a covariate in analyses.

## Power analysis

4

We conducted a power analysis where tests of hypothesized differences were performed using linear contrast analysis within the framework of random effects general linear models (GLMs). For these single degree of freedom tests, power was approximated using two-tailed independent sample *t*-test in G∗Power 3.1.9.7. For the moderator analysis examining sex-specific associations between education opportunity and the primary outcome, brain health, at an alpha .05/2 markers of brain health = .025, 150 participants per group (mobile/static 1:1 ratio female:male) provided adequate power (80%) to detect an effect size difference as small as Cohen's d = 0.36 (tcrit = 2.25, noncentrality parameter = 3.10), if it exists. This sample size also provided 80% power to detect associations as little as f^2^ = .04 (multivariate linear regression for moderated mediation analyses, Crit F = 2.24, noncentrality parameter = 13.07).

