### Recruitment & eligibility

3.1

The demographics of the original RISE-Up Study have been described extensively elsewhere (Wong et al., 2022; Dudovitz et al., 2018), but broadly consisted of 1270 participants (52.6% female, 47.4% male, median age 14.2) who were entering 9th grade in Fall 2013 or Fall 2014. Participants for the original study were largely recruited from and are representative of low-income neighborhoods in Los Angeles, with 1137 (89.5%) identifying as Latino (Dudovitz et al., 2018), and all applied for high-achieving charter high school admission lottery, with 694 students (54.6%) being admitted on the basis of random lottery (intervention/mobile group) and 576 students (45.4%) on the waiting list (control/static group). Recruitment for the RISE-Up-EA+ extension study is dependent upon previous participation in the RISE-Up-EA follow up study, which is ongoing (see Fig. 1 for a timeline of study phases). A subsample of 300 participants aged 24-26 years old who previously consented to follow-up contact will be included in the extension study. Detailed contact information has been maintained for prior participants, enabling digital communication via text message and email. Interested respondents will schedule a phone screening, during which a study coordinator will administer a brief screening interview and obtain informed consent. During this phone screen, the research staff will also explain procedures for the extension study. Participants who meet eligibility criteria for the study (including MRI safety screening) and agree to participate will be scheduled for a three and a half hour on-site in-person session at the University of California, Los Angeles (UCLA) where they will complete a magnetic resonance imaging (MRI) scan, behavioral tasks, cognitive assessments, and will be administered biospecimen samples (see Fig. 3 for session flow). Prior to their in-person session, participants will be consented and will be administered questionnaires to complete remotely or they will have the opportunity to complete questionnaires at the in-person session. The protocol for this study has been approved by the Medical Institutional Review Board of the University of California, Los Angeles (IRB#24-000281).

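### If the planning level of .025 per brain-health marker is carried into the analysis, it is valid but less efficient than Holm's step-down across the same two markers

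*Protocol article*

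**What the plan says.** Section 4 (Power analysis) treats brain health as the primary outcome, with the aim of examining "sex-specific associations between education opportunity and the primary outcome, brain health". It counts two markers of brain health and gives each half of the 5% level: "at an alpha .05/2 markers of brain health = .025, 150 participants per group". The calculation is an approximation: "power was approximated using two-tailed independent sample *t*-test in G∗Power 3.1.9.7". The result is that the sample "provided adequate power (80%) to detect an effect size difference as small as Cohen's d = 0.36", with critical t 2.25 and noncentrality 3.10. The total of 300 is repeated in section 3.1 (Recruitment & eligibility): "A subsample of 300 participants aged 24-26 years old who previously consented to follow-up contact will be included in the extension study".

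The article gives no other multiplicity level for these markers and mentions no step-down or sequential procedure. Section 4 does not say which two measures are meant. Section 3.2.3 (Neuroimaging) describes several that could qualify.

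**The concern.** An equal split holds each marker to .025 whatever the other shows. Holm's procedure compares the smaller p-value with .025 and, if that rejects, the larger with .05. It rejects everything the equal split rejects and sometimes more, and it holds the familywise error at 5% under any correlation between the markers. If the planning level becomes the testing rule, the study gives up some power on its primary outcome and gains little in return. The recruitment target is fixed at 300 from an existing cohort, so efficiency in the analysis is one of the few ways left to gain power.

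**Working it through.** **Inputs from section 4.** Two-sided t-test, 150 v 150 (298 degrees of freedom), .05/2 = .025 per marker, d = 0.36, 80% power.

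**Assumptions, not in the article.** The correlation r between the markers, taken from 0 to 0.8. The effect on the second marker, taken as d = 0.36, 0.20 or 0.

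**Step 1: reproduce the plan's figure.**
- Critical t for two-sided .025 with 298 df: 2.253 (stated 2.25).
- Noncentrality at d = 0.36: 0.36 × √(150/2) = 3.118. Power from the noncentral t: 80.6%.
- At exactly 80% power the detectable d is 0.3575, with noncentrality 3.096. These round to the stated 0.36 and 3.10, so the figure reproduces.
- The same test at .05 (critical t 1.968) has power 87.4%.

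**Step 2: Holm in closed form, independent markers, both at d = 0.36.** Let a = 0.8060 (power at .025) and b = 0.8744 (power at .05).
- Per marker: a + (b − a) × a = 0.8060 + 0.0684 × 0.8060 = 0.861. Equal split: 0.806.
- Both markers: b² − (b − a)² = 0.7646 − 0.0047 = 0.760. Equal split: a² = 0.650.
- At least one marker: 1 − (1 − a)² = 0.962 under either rule, because Holm's first step is the equal split's test.

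**Step 3: correlated markers, both at d = 0.36.** Two million simulated pairs of t statistics per setting:

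| r | Per marker, split → Holm | Both, split → Holm | At least one, either rule |
|---|---|---|---|
| 0 | 80.6% → 86.1% | 65.0% → 76.0% | 96.3% |
| 0.3 | 80.6% → 85.6% | 67.5% → 77.4% | 93.7% |
| 0.5 | 80.6% → 85.1% | 69.5% → 78.6% | 91.7% |
| 0.8 | 80.6% → 84.3% | 73.6% → 81.1% | 87.6% |

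**Step 4: unequal effects.**
- Second marker at d = 0.20: its power rises from 30.3% to 38.8% (r = 0) or 40.5% (r = 0.8). The first marker gains 0.1 to 2.1 points.
- Second marker with no effect: for independent markers the first gains (b − a) × 0.025 = 0.0684 × 0.025 = 0.0017, about 0.2 points. By simulation the gain is 0.1-0.2 points across the range of r.

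**Step 5: error rates.**
- Both nulls true: the familywise error is the same under both rules. For independent markers it is 1 − 0.975² = 4.94% (simulated 4.95%), and at r = 0.8 it is 4.0%.
- One marker null, the other at d = 0.36, independent: the null marker is falsely rejected with probability 0.025 + 0.025 × 0.806 = 4.5% under Holm, against 2.5% under the split. The simulated value falls to 3.9% at r = 0.8. All are below 5%.

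**The case against.** The strongest objection is that .025 appears in a power section, in the past tense, as an input to an approximate calculation. The article does not say that each marker will be tested at .025 regardless of the other. A study already planning Holm could print the same sentence, since Holm's first step uses .025, and an analysis plan that is not shown may specify a step-down. This stands, and it makes the point conditional. It does not remove it: an equal split is the only rule in the text shown, and the split never rejects more than Holm.

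The equal split is also valid, so nothing is stated wrongly. That stands too.

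Holm has small costs. Simple simultaneous confidence intervals do not match a step-down test, and the error rate for a single null marker can rise from 2.5% to about 4.5%. Both are real, but the second stays within the 5% familywise limit.

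A reader might infer that a conclusion about brain health needs both markers to be positive, which would make the both-marker gain decisive. The document does not say so, either in hypothesis H1 or in section 4. If it did, each marker could be tested at .05 without adjustment, giving 0.8744² = 76.5% for independent markers against Holm's 76.0%, so Holm would not be the natural remedy.

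A reader might also infer that Holm helps with whether a 150 v 150 comparison can power a test of moderation by sex. That is a separate issue, and Holm does not repair it.

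**Conclusion.** The point holds as an optional efficiency gain. The stated level is valid and the 80% at d = 0.36 is correctly computed. If the equal split is carried into the analysis, Holm would raise power per marker by 3.7 to 5.5 points and power to show both by 7.5 to 11 points, with the same sample and the same 5% familywise limit. These sizes assume that both markers have d = 0.36 and that their correlation lies between 0 and 0.8; the article gives neither a second effect nor a correlation. The chance of at least one positive marker is unchanged in every case, and the gain nearly vanishes if only one marker has an effect. The text does not support reading this as an error in the plan, or as proof that a step-down has been ruled out.

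**What to change.** State in the analysis plan that the two brain-health markers, named in advance, will be tested by Holm: the smaller p-value against .025 and, if that rejects, the larger against .05. If an existing analysis plan already says this, it need only be confirmed. Keep 80% power at d = 0.36 as the conservative planning figure, because the first step still uses .025. Report .025-level confidence intervals alongside the step-down results.

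The cost is one sentence and no extra participants. Recruitment is described as ongoing (Fig. 1 caption), so the rule should be fixed before outcome data are analysed; adopted later, it would look data-driven. Holm, like the equal split, is sound only if the two markers are chosen beforehand.

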
**Fig. 1 fig1:**
[figure not shown]
*Timeline of RISE-Up Study Phases*. 1270 participants were recruited and enrolled at baseline in the RISE-Up High School Study and were followed throughout grades 9-12. 977 participants continued with the RISE-Up Transition to Adulthood Study and were followed through age 24. The RISE-Up into Early Adulthood Study phase is ongoing with the goal of recruiting 750 participants ages 24-28 that previously participated in the baseline study. The RISE-Up Early Adulthood Extension Study is ongoing with the goal of recruiting 300 participants ages 24-26 from the RISE-Up EA Study. Created in https://BioRender.com.

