###### Magnetic resonance spectroscopy (MRS)

3.2.3.3.1

Neurometabolic data will be characterized with single voxel (SV) magnetic resonance spectroscopy (MRS) in three different regions: dorsal anterior cingulate cortex (dACC), right hippocampus, and left hippocampus. The dACC was chosen as a region of interest because of its involvement in cognitive control and it has been previously implicated in MRS studies assessing metabolic alterations in those with mild cognitive impairment and AD. (Huang et al., 2017; Chen et al., 2025) The hippocampus was chosen as a region of interest given that it is a critical region for learning and memory and it has been shown to be a sensitive and central region for AD, particularly for disease pathology, early disease diagnosis, as well as for disease progression (Song et al., 2021). Additionally, prior MRS studies have observed significant metabolite alterations in the hippocampus in AD patients compared to controls, including metabolites that are indicators of neuroinflammation (Song et al., 2021). In line with MRS expert consensus (Wilson et al., 2019) for data acquisition at 3T *in vivo*, we will implement a short echo time semi-LASER (sLASER) sequence (Oz and Tkáč, 2011; Deelchand et al., 2021) to be used with an automated B_0_ and B_1_ shimming calibration protocol (Gruetter and Tkác, 2000; Deelchand et al., 2022) to improve acquisition of high-quality MRS data. LCModel (Provencher, 2009) will be used to fit and quantify all estimated metabolite concentrations with total creatine acting as an internal reference standard. Quality assurance procedures include ensuring all metabolite estimations that will be used for analysis have relative Cramer-Rao lower bounds (CRLBs) < 25%. GM and WM tissue percentages will also be calculated within each voxel to correct for total tissue content.

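### Both 80% power figures in section 4 need usable data from all 300 recruited participants and leave almost no margin for missing scans or samples

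*Protocol article*

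**What the plan says.** The Fig. 1 legend describes the extension study as ongoing "with the goal of recruiting 300 participants ages 24-26 from the RISE-Up EA Study". Section 3.1 gives the same number: "A subsample of 300 participants aged 24-26 years old who previously consented to follow-up contact will be included in the extension study".

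Section 4 uses that number as the analysed sample. The brain-health contrast is a two-tailed two-sample t-test "at an alpha .05/2 markers of brain health = .025", with "150 participants per group (mobile/static 1:1 ratio female:male) provided adequate power (80" per cent) for d = 0.36, critical t 2.25 and noncentrality 3.10. The same sample is said to give 80% power for f² = .04 in the regression for moderated mediation, with critical F 2.24 and noncentrality 13.07. Section 4 mentions no allowance for unusable or missing values.

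Three measurement sections describe steps at which a value may be absent:

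- **Spectroscopy (3.2.3.3.1):** quality assurance includes "ensuring all metabolite estimations that will be used for analysis have relative Cramer-Rao lower bounds (CRLBs) < 25" per cent.
- **Blood (3.2.5.1):** if no sample was taken in the parent follow-up study, "participants will have the option to provide blood samples at this extension study".
- **Stool (3.2.5.2):** "These stool samples will be collected at home and mailed back to the lab".

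Aim 3 in section 2 treats brain health, inflammatory blood markers and the microbiome as parallel mediators in one moderated model for general cognitive ability.

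**The concern.** If the number recruited equals the number analysed, the printed power holds only when every recruit yields every value that the analysis needs. The measurement sections allow for less than that. Aim 3 is the most exposed, because it draws on three separately collected sources in the same person.

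What is at stake is how a null result is read. If sex moderation or mediation is not found, readers will ask what size of effect the study could have detected. The answer printed in section 4 is the best case, and for the regression it has also been rounded down.

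**Working it through.** **Inputs.** From section 4: 150 per group, two-sided alpha .025, d = 0.36, critical t 2.25, noncentrality 3.10; then f² = .04, critical F 2.24, noncentrality 13.07. From Fig. 1 and section 3.1: 300 recruited. The article gives no loss rates and no number of predictors.

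**Step 1. Reproduce the t-test figure.** Noncentrality = d × √(n/2), with df = 2n − 2.
- n = 150 per group: critical t = 2.253, as printed.
- d = 0.36: 0.36 × √75 = 3.118, power 80.6%.
- Power of exactly 80%: d = 0.3575, and 0.3575 × √75 = 3.096, which matches the printed 3.10.

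**Step 2. Reproduce the regression figure.** Noncentrality = f² × N, with p and N − p − 1 degrees of freedom.
- N = 300 and alpha .05: p = 4 gives critical F 2.402, p = 5 gives 2.245, p = 6 gives 2.130. Only p = 5 fits the printed 2.24, so five numerator degrees of freedom are inferred.
- With p = 5, 80% power needs a noncentrality of 13.07, as printed. Hence f² = 13.07 / 300 = .0436.
- At exactly f² = .04 the noncentrality is .04 × 300 = 12.0 and power is 76%, with nobody lost.
- The noncentrality alone hardly depends on N (13.08 at N = 285), but 13.08 / 285 = .046 would not round to .04. The printed set therefore fits N = 300, as the text says.

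**Step 3. Find the margin.** Power at d = 0.36 is 80.6% with 150 per group, 80.0% with 148 and 79.7% with 147. Since 147/150 = 0.98, the 80% claim fails at a 2% loss, or six people in all. The regression has no margin: 80.0% at f² = .0436 with N = 300, and less with any loss.

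**Step 4. Illustrate with assumed losses, equal in both groups.** For the t-test the loss is of usable brain measures. For the regression it is the overall loss for the joint model, if only complete records counted. Group sizes are rounded down.

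| Assumed loss | Per group / N | Power at d = 0.36 | Detectable d (80%) | Power at f² = .0436 | Detectable f² (80%) |
|---|---|---|---|---|---|
| 0% | 150 / 300 | 80.6% | 0.358 | 80.0% | .0436 |
| 5% | 142 / 284 | 78.2% | 0.368 | 77.4% | .0461 |
| 10% | 135 / 270 | 75.9% | 0.377 | 74.9% | .0485 |
| 20% | 120 / 240 | 70.3% | 0.400 | 68.8% | .0547 |

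The table takes the article's two tests as given. It does not examine whether a two-group t-test or an overall F test is the right stand-in for moderation or mediation.

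**The case against.** The strongest reply is that no loss is documented. Small losses hardly matter: the detectable d still rounds to 0.36 down to 144 per group, a 4% loss. The loss routes are also softer than they may look. The blood option is a second chance for people not sampled in the parent study, so it reduces missing values. The spectroscopy limit applies to each metabolite estimate, not to a whole scan, and section 4 does not say which two brain-health markers it means, so a failed estimate need not remove anyone from the primary contrast. Mailing stool from home is a collection method, and nothing says how many kits fail to come back. MRI safety exclusions and moves out of state act before enrolment and do not reduce the 300. All of this stands, and it limits the point to a missing margin.

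Three stronger readings are tempting, and the article does not support them:

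- **That structural scans are removed.** Section 3.2.3.1.1 mentions quality control procedures but states no exclusion rule.
- **That Aim 3 will discard anyone with a missing mediator.** The article does not specify complete-case analysis. How missing values are handled is commonly left to an analysis plan, which is not shown here.
- **That scan, blood and stool losses multiply independently and should be set against the printed f² of .04.** Independence is not documented, and losses that cluster in the same people would leave a larger joint sample. Part of any gap from .04 is rounding, so the like-for-like baseline is .0436.

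What the reply does not remove is that recruited and analysed numbers are identical, and that both figures sit at the edge of 80%.

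**Conclusion.** The point holds as a planning assumption that section 4 does not state. Both 80% figures require 300 analysable participants, the same as the recruitment goal, with a margin of about 1% for the t-test and none for the regression. Separately, and with no assumption about loss, the printed f² of .04 is rounded down from .0436 and corresponds to 76% power, given the inferred five degrees of freedom.

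A reader might infer that the study is shown to fall short of 80%. It is not: the shortfall depends on a usable fraction that the article does not give. It is about 2 to 3 percentage points at 5% loss, about 5 at 10%, and 10 to 11 at 20%. For the regression these are complete-record figures; a method that uses partial records could recover some of that loss, but would not replace missing brain measures in the primary contrast.

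**What to change.** Keep 300 participants and amend section 4 in three places:

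1. Print the regression effect as f² = .044, and state the number of predictors and the alpha.
2. State the expected usable fraction for the brain-health markers, and separately for brain, blood and stool measures jointly in Aim 3, with the source of each assumption.
3. Give the detectable effects at those numbers. For example, if 10% to 20% are assumed unusable: d = 0.38 to 0.40 for brain health, and f² about .049 to .055 for the regression.

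If the Aim 3 analysis will use partial records, say that the regression values are complete-record figures.

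The cost is a few restated figures and somewhat less favourable detectable effects. No procedure changes and no extra recruitment is needed.
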